## Methods/design

### Study objectives

The present study aims to (a) determine the potential clinical impact of the NEAT program on clinical symptoms and function, from pre- to post-intervention and at long-term follow-up (12 months after treatment completion), and (b) explore the potential impact of the NEAT program on functional and structural brain recovery, from pre- to post-intervention.

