**Fig. 1 Fig1:**
[figure not shown]
CONSORT flow diagram. The flow chart depicts participant progression through the study from the initial enrolment to allocation, follow-up, and finally analyses of their data stages. Planned sample size, *n* = 64; to be enrolled, *n* = 80. Forty participants will be enrolled in each arm (expected to be 8 dropouts in each arm from pre- to post-intervention on average)

The trial was approved by the Western Institutional Review Board (approval number: 20181028, 1-1141403-1) and registered in ClinicalTrials.gov on 22 April 2019 with NCT03922646 as ClinicalTrials.gov identifier no.; amendments have been made to the protocol since the original submission to ClinicalTrials.gov. The study is funded by the Oklahoma Center for Advancement of Science and Technologies (OCAST) [name] [HE], principal investigator [PI], and [name] [RA] as co-investigator [CI].

As this study is considered a “no or minimum risk” trial, there is no independent data monitoring committee (DMC) assigned for this trial. Trial investigators will monitor the data collection process, fidelity of the intervention, and integrity of protocol implementation on regular weekly basis meetings with the research staff. There is no plan for interim analyses, and there are no anticipated formal stopping rules for the trial as there are no anticipated problems that could be detrimental to the participants or the study integrity. The data that will be collected in this study will be available from the principal investigator on reasonable request.

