### Sample size calculation

With total enrollment of *N* = 80 and an estimated 20% attrition rate, we anticipate having complete data at our primary endpoint (post-treatment) for 32 subjects per group or 64 in total. Due to cluster randomization, the effective sample size will be *n* = (*mk*)/[1 + *ρ*(*m* − 1)] where *m*, *k*, *ρ* are the number of subjects per cluster, the number of clusters, and the intra-cluster correlation, respectively [24]; here, *k* = 4, and on average, *m*= 8 (80% of 10) per cluster. Considering a range of 0.05 to 0.3 for *ρ*, *n*_Eff_ will be somewhere between 10.3 and 23.7 per group. This effective sample size will provide a precision of *t*_*n*-1,1-*α/2*_/√*n* or 0.43–0.70, times standard deviation as margin of error at 95% confidence for a continuous measure (self-reported drug craving), and 80% power to detect large effect sizes (*d* = 0.83 to 1.3) for group differences in pre to post or pre to follow-up changes at a two-sided 5% significance of a 2-sample *t* test. While we may be underpowered to detect small to medium effects, the current pilot study will be crucial for informing the viability of the intervention and for estimating power for future, larger clinical trials.

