**Fig. 4 Fig4:**
[figure not shown]
Schedule of enrollment, interventions, and assessments. This figure indicates the assessments or interventions completed for screening, pre-intervention, weekly during the completion of the intervention, post-intervention, and 3- and 6-month follow-up. Participants are randomized in groups of 9–12 to complete either neuroscience-informed psychoeducation (NEAT) or active control intervention. *OCDUS*, Obsessive Compulsive Drug Use Scale; *ASI*, Addiction Severity Index; *CDDR*, Customary Drinking and Drug Use Record; *DDQ*, Desire for Drug Questionnaire; *TEQ*, Traumatic Events Questionnaire; *BIS/BAS*, Behavioral Inhibition System/Behavioral Approach Scale; *UPPS-P*, UPPS Impulsive Behavior Scale; *DERS*, Difficulties in Emotion Regulation Scale; *PROMIS*, Patient-Reported Outcomes Measurement Information System; *SES*, Services Engagement Scale; *CEST*, Client Evaluation of Self and Treatment; *HRS*, Homework Rating Scale; *WAI*, Working Alliance Inventory; *PROMIS-CA*, PROMIS Cog Abilities; *PROMIS-CG*, PROMIS Cog General

Biological specimens (blood and oral and mouth microbiome) data will be collected in the baseline for further exploratory analysis on the predictive role of biomarkers on response to interventions. Less than 150 mL of blood will be collected per subject, which is well within the safety limit of ~ 450 mL per blood draw. Blood will not be drawn from subjects with a hematocrit below 30%. A trained phlebotomist will obtain blood samples in the morning of one of the visits, or at a time convenient for the participant. Participants will also be asked to provide microbial samples during the biomarker session.

For blood samples, plasma, serum, PBMCs, and genetics will be transported to and processed at the University of Oklahoma Integrative Immunology Center (IIC) Laboratories. Plasma, serum, and genetic samples will be stored in secure freezers at − 80 °C. Freezers will be maintained in a specially equipped room with emergency backup power and an automated telephone alarm system that is programmed to call in case of failure. Additional aliquots of samples will be stored at − 80 °C should repeat analyses be required at a later date. PBMCs will be stored in liquid nitrogen dewars with liquid level monitors and alarms in a secure room at the University of Oklahoma IIC Laboratories.

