### Statistical analysis

Categorical variables will be summarized by frequency and proportion, and continuous variables by mean and standard deviation (SD), or by median and inter-quartile range if the distribution, appeared skewed even after simple (e.g., log) transformations, for all participants and for participants in each treatment arm. Data normality will be evaluated by quantile-quantile (QQ) plot and Shapiro-Wilk test.

Treatment effects will be compared by the intention-to-treat (ITT) principle, i.e., all subjects who were randomized will be included in the final analysis, regardless of their adherence to any of the interventions. In order to detect changes in the variables recorded for the primary and secondary outcomes, mixed-effects model analyses will be performed using fixed-effects of time (pre-, post-intervention time points) as a within-subject factor and condition (intervention vs. control) as a between-subject factor; within-subject dependency will be captured by either random cluster and/or subject intercepts or within-subject correlation structure (e.g., 1st-order autoregressive or exponential power), whichever Akaike or Bayesian information criterion (AIC or BIC) favor. Mixed-effects models allow using all available observations and, without the need of imputation, provide unbiased estimates under the missing at random mechanism, a plausible assumption for randomized trials, and are known to be more powerful than any ad hoc imputation [59]. We include age and IQ as covariates. The inclusion of other covariates will be determined by AIC and BIC. Subgroup analyses will be conducted according to the baseline neuropsychological and fMRI characteristics. Significance level will be set at 0.05 level for the primary outcome and hypothesis; Bonferroni correction will be applied to all pre-post comparisons for all secondary outcomes, and Benjamini-Hochberg’s procedure to control false discovery rate at 5% level for all the exploratory analyses. For each outcome measure (primary, secondary, and exploratory), effect sizes of Cohen’s *d* and *f* will be computed. The effect sizes, along with the attrition rate at each time point, can be used to guide future study design.

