Fewer studies before have indicated the effectiveness of metacognitive awareness and cognitive rehabilitation interventions in alcohol and substance users, in terms of craving control, improved cognitive functions, and better treatment outcomes (e.g., treatment adherence, length of abstinence) [65–71]. Although in all these studies, the promising results are viewed as a sign of improved regulatory control of top-down system over bottom-up system, but no evidence exists for underlying neural substrates. Therefore, our study is the first attempt that applies a broad range of assessments including neural components to monitor the effect of a cognitive rehabilitation program in substance users. We also consider the effect of the intervention on real-world functioning (e.g., craving management and social and emotional competency) to provide more data on the ecological validity. Randomized allocation of patients in two groups, employment of an active control condition, blinding outcome assessors, using a fully manualized intervention, and monitoring the long-term effect of intervention during 1-year follow-up are the most important strengths of the present study.

In this study, we are expecting to face the following limitations: (1) participant withdrawal due to schedules changing or phasing up in the program, (2) scheduling of other appointments (i.e., visiting a physician) during Brain Gym times, (3) participants not completing suggested homework or not fill the brain planner, (4) participants absconding from the WiR program or being terminated from the program, and (5) follow-up problem and lack of data about those participants once they are discharged from WiR.

To conclude, the effects of a multi-component neurocognitive rehabilitation and awareness program termed “Neurocognitive Empowerment for Addiction Treatment” (NEAT) on psychological, neurocognitive, and structural and functional neuroimaging measures will be examined in a group of female opioids and or methamphetamine users in the context of addiction recovery. If the results of this study prove the efficacy of NEAT as it is expected, then a larger trial will be needed to provide confirmatory evidence to support the next step for transferring the intervention to the clinical practice and embedding NEAT into the routine therapeutic programs as a supplementary intervention.

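### The 80% power stated for pre-to-follow-up changes rests on the completer count at week 8, so it holds only if nobody is lost afterwards

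*Protocol article*

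**What the plan says.** The Sample size calculation section starts from 80 enrolled, takes off 20% attrition, and expects 32 per arm with complete data at the primary endpoint, which it identifies as post-treatment. With four groups per arm this is 8 completers per group. An ICC of 0.05 to 0.3 then gives an effective sample size of 23.7 down to 10.3 per arm. From this the section claims "80% power to detect large effect sizes", d = 0.83 to 1.3, "for group differences in pre to post or pre to follow-up changes".

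The Fig. 1 caption dates the attrition: "expected to be 8 dropouts in each arm from pre- to post-intervention on average". That is 8 of 40, the whole of the 20%.

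The Design section puts post-intervention at week 8 and the follow-up visits at weeks 20, 32 and 56. The Discussion lists, among expected limitations, participants absconding or being terminated from the recovery program, and "follow-up problem and lack of data about those participants once they are discharged from WiR". It gives no rate.

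**The concern.** One completer count serves two contrasts measured at different times. The attrition allowance is used up by week 8, and nothing is set aside for the 48 weeks between then and the last visit. The power statement for follow-up therefore assumes complete retention after week 8, while the Discussion of the same article expects data to be missing at follow-up.

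At stake is how follow-up results will be read. Study objectives includes clinical impact "at long-term follow-up (12 months after treatment completion" in its first aim. A reader who takes the power statement at face value would treat a null follow-up result as better supported than it is. The article also presents the trial as a basis for powering a larger study, so later planners may reuse the follow-up figure.

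**Working it through.** **Inputs.** From Sample size calculation and Design: two-sided 5% two-sample t test, 80% power, k = 4 groups per arm, 10 enrolled per group on average, m = 8 completers per group at week 8, ICC (rho) 0.05 to 0.3. Retention after week 8 is not given, so total loss of 30%, 40% and 50% by the follow-up visit is assumed here, spread evenly over groups. The ICC range and the standardised scale are kept as in the article.

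**Formulas.** Effective sample size per arm: n_eff = mk / [1 + rho(m - 1)]. Detectable d: the value at which a non-central t with 2·n_eff - 2 degrees of freedom and non-centrality d·√(n_eff/2) exceeds the two-sided 5% critical value with probability 0.80.

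**Step 1: reproduce the article at week 8 (m = 8).**
- rho = 0.05: n_eff = 32 / 1.35 = 23.70; margin of error 0.425 SD; detectable d = 0.832.
- rho = 0.3: n_eff = 32 / 3.1 = 10.32; margin of error 0.700 SD; detectable d = 1.301.

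These match the stated 23.7 and 10.3, 0.43 and 0.70, and 0.83 and 1.3. The week-8 calculation is right.

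**Step 2: repeat with fewer completers.** Only m changes, to 10 × (1 - total loss).

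| Total loss | Completers per arm | Lost per arm after week 8 | rho | n_eff | Detectable d at 80% power | Power at the stated d |
|---|---|---|---|---|---|---|
| 20% (article) | 32 | 0 | 0.05 | 32/1.35 = 23.70 | 0.832 | 79.9% at 0.83 |
| 20% (article) | 32 | 0 | 0.3 | 32/3.1 = 10.32 | 1.301 | 79.9% at 1.3 |
| 30% | 28 | 4 | 0.05 | 28/1.30 = 21.54 | 0.874 | 75.8% |
| 30% | 28 | 4 | 0.3 | 28/2.8 = 10.00 | 1.325 | 78.5% |
| 40% | 24 | 8 | 0.05 | 24/1.25 = 19.20 | 0.929 | 70.7% |
| 40% | 24 | 8 | 0.3 | 24/2.5 = 9.60 | 1.356 | 76.6% |
| 50% | 20 | 12 | 0.05 | 20/1.20 = 16.67 | 1.002 | 64.1% |
| 50% | 20 | 12 | 0.3 | 20/2.2 = 9.09 | 1.399 | 74.0% |

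**Step 3: why the ICC matters.** With four groups per arm, n_eff cannot exceed k/rho however large the groups are: 4/0.3 = 13.3 against 4/0.05 = 80. At the high ICC most of the information lies in the number of groups, so losing members costs little. At the low ICC it costs more.

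**The case against.** The strongest defence is that no calculation is wrong: every figure reproduces at week 8, and the problem is the reach of one phrase. That is correct, and it makes this a point about scope rather than arithmetic.

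Second, the loss rates are assumed. Follow-up visits are paid. Women may join up to 6 months after entering the program and graduate after 17 months on average, and week 56 is about 13 months after baseline, so it falls roughly 13 to 19 months after program entry. Many could still be in the program for much of follow-up. This weakens any particular rate but does not support zero further loss: absconding and termination are listed separately from discharge, and the article expects missing follow-up data.

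Third, all the recalculated effects are still large, and the article already calls itself a pilot that may be underpowered for small to medium effects. That limits the consequence but does not make the follow-up power figure right.

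A reader might also infer more: that the 12-month part of the first aim has no analysis at all, because the only model described has "fixed-effects of time (pre-, post-intervention time points) as a within-subject factor", or that follow-up scores will be discarded. The article does not support either inference. That model is written for the primary and secondary outcomes, and both are defined as changes from before to after the intervention, so model and outcomes agree. The hypotheses that reach into follow-up, on mental health symptoms and relapse, are declared exploratory, with false discovery rate control and effect sizes specified. The article names no model covering the 12-month part of the aim, but a condensed article may leave that to a fuller document not shown, and nothing says later scores are dropped.

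**Conclusion.** The point holds as one of scope. The statement of 80% power at d = 0.83 to 1.3 is justified for the pre-to-post contrast. It is not justified for pre-to-follow-up changes, because it uses the week-8 completer count and so assumes no later loss, contrary to the article's own expectation.

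The direction is certain for any loss after week 8. The size is not fixed by the article. Under the assumed 30% to 50% total loss, the lower end of the detectable range moves from 0.83 to between 0.87 and 1.00, and the upper end from 1.30 to between 1.33 and 1.40. Power at the stated effects drops by about 4 to 16 percentage points at ICC 0.05 and about 1 to 6 points at ICC 0.3. This rests on even loss across groups and on the article's own method and ICC range. The primary pre-to-post comparison is unaffected.

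**What to change.** Either limit the 80% power sentence to the pre-to-post contrast by removing the reference to follow-up changes, or keep follow-up and give it its own line: an assumed retention at the visit concerned, the resulting completers per group and effective sample size, and the detectable d. Without a basis for one retention figure, a short range such as the table above would do. If the follow-up comparisons are meant as exploratory estimates, saying so in the sample size section would remove the need for a follow-up power figure.

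The cost is a change of wording. No visit, measurement or enrolment target changes. The stated follow-up sensitivity becomes less favourable.

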### Recruitment

Study participants will be recruited through the WIR program at Family and Children’s Services. Flyers will be provided to the clinic program staff to be given to potential subjects. The research team may also discuss the study to the groups of patients (i.e., when gathered for a class). The research team will be available at WIR on a regular basis to discuss the study privately with subjects interested in the study. The WIR staff will not be present during these individual meetings in order to increase confidentiality and ensure that subjects are making an informed decision to participate. All efforts will be made to ensure that the recruited subject population closely resembles the ethnic and racial composition of the WIR program. The enrolled participants then will give a written informed consent to one of the principle investigators (PI) or research coordinator (RC) in a private interview/exam room at LIBR or WIR. Family members will be allowed to be present and discuss the consenting process with the participant if requested. In this session, it will be emphasized that participation is strictly voluntary and that they have the right to withdraw at any time without penalty. It will be emphasized that the information provided during the course of the study will have no impact on participants’ treatment and care provided by WIR or other programs and clinics, their experience at correctional facilities, or on any court processes or decisions. Follow-up meetings with the WIR staff and directors will be held to make sure the reasonable number of recruitments will happen to meet the planned sample size.

Note that participants will be monetarily compensated for their time of participation in self-report, behavioral, and neuroimaging assessment. Each participant will be also provided with a gift card ($10–15 per session) to compensate completing intervention session assessments.

There are three follow-up assessment sessions 3, 6, and 12 months after completion of the intervention with urine drug test and questionnaires. Participants will be compensated for their time for the follow-up assessments as well.

### Randomization and blinding

All consented participants will receive NEAT or other active, but non-essential regularly scheduled programming at WIR coinciding with the same timeframe. Randomization will be happening in the group level, and groups of 9–12 participants will be randomly allocated to intervention conditions (study arms). This randomization will be conducted in blocks of 4 groups. The randomization will be determined prior to enrolling any subjects using computer-generated allocations.

The randomization codes will be generated by a statistician not involved in enrollment or delivery of interventions and will be kept in a secure computer file with controlled access. The research staff involved in the conduct of interview-based assessments (e.g., MINI, PRISM-5) will be blinded to the intervention condition. Participants and all research staff are kept blind to their intervention condition until completion of all baseline assessments. However, due to the nature of the intervention, participants and research staff involved in providing interventions will not be kept blind to the interventions after completion of baseline assessments. Research investigators (who are unblinded) will be involved in both delivering the intervention and doing the data analysis; therefore, outcome analysis will not be blinded.

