### Design

This is an assessor-blinded, two-arm, parallel-group, randomized controlled clinical trial formulated in accordance with the Consolidated Standards of Reporting Trials (CONSORT) 2010 guidelines (supplementary file 1). This protocol was written using the Standard Protocol Items: Recommendations for Interventional Trials (SPIRIT) guidelines, and the SPIRIT checklist is provided in supplementary file 2. Eighty participants will be recruited in eight groups. Groups will be randomly allocated to the intervention (*n* = 40) and control (*n* = 40) groups in blocks of 4 in a 1:1 ratio. All 80 participants will receive treatment-as-usual (TAU). Those subjects allocated to the intervention group will receive TAU but will complete NEAT in lieu of nonessential aspects of the TAU program that do not explicitly target neurocognitive function (e.g., culinary or legal education classes). Thus, both NEAT and TAU groups received similar amount (e.g., intensity, duration, frequency) of intervention. Self-report, interview-based, and neuroimaging assessments will be performed before (pre; week 0), during intervention (from week 1 to week 7), after the intervention period (post; week 8), and/or after a follow-up period (3, 6, 12 months; weeks 20, 32, 56, respectively). Interview-based assessments were conducted by a trained clinical practitioner blind to the allocation of participants. Figure 1 summarizes the full design of the trial in accordance with the CONSORT flow diagram.

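### With eight groups allocated 1:1 in fixed blocks of four and earlier arms open, two to four arms can be deduced before consent if groups form one after another, so pre-baseline blinding cannot be guaranteed

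*Protocol article*

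**What the plan says.** The Design section gives the scale and the ratio: "Eighty participants will be recruited in eight groups", with allocation to intervention and "control (*n* = 40) groups in blocks of 4 in a 1:1 ratio". The section Randomization and blinding gives the unit, "Randomization will be happening in the group level, and groups of 9–12 participants will be randomly allocated to intervention conditions (study arms"), and repeats the block: "This randomization will be conducted in blocks of 4 groups". No other or varying block size is mentioned.

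On concealment, the same section says: "The randomization will be determined prior to enrolling any subjects using computer-generated allocations". It adds: "The randomization codes will be generated by a statistician not involved in enrollment or delivery of interventions", and says that the codes are kept in a controlled-access file.

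On blinding, it says: "Participants and all research staff are kept blind to their intervention condition until completion of all baseline assessments". After that point, participants and the staff providing the interventions are not blind. The investigators are described as unblinded and as taking part in both delivery and analysis.

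The Recruitment section has women give "written informed consent to one of the principle investigators (PI) or research coordinator (RC"). It also describes flyers handed out by programme staff and private meetings with the research team. Nothing in the article says whether the eight groups are formed singly, in pairs or a block at a time.

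**The concern.** In a group-randomised trial, concealment has to protect the recruitment of individuals into a group as well as the group's own assignment. A small fixed block combined with open earlier groups can defeat this without any leak of the list, because the remaining arms can be worked out from those already seen. Anyone who knows the block size and the arms of earlier groups in the block can do so.

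Recruiters could then, knowingly or not, encourage some women to join the current group and others to wait. Participants are unmasked after baseline, and the primary outcome is self-reported craving. The model in Statistical analysis fixes age and IQ as covariates and uses baseline as a time point. Neither removes a difference between groups in, say, motivation to change. Selection bias of this kind is not reflected in the margin of error in the sample size section, and the trial's effect sizes are meant to guide future trials.

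**Working it through.** **Inputs.** Eight groups, 1:1, blocks of four (Design; Randomization and blinding), so two blocks, each with 2 NEAT (N) and 2 control (C) groups. Four groups per arm (Sample size calculation). Each group's arm is open once its baseline is complete (Randomization and blinding). Formation order is not stated, so three cases are shown.

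**The plan's own figures.** The article gives no figure for predictability. Its effective sample size per arm reproduces: 8 × 4 / (1 + 0.05 × 7) = 23.7 and 8 × 4 / (1 + 0.3 × 7) = 10.3. The point made here does not affect these.

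**Rule.** A group counts as predictable when the arms already revealed in its block leave only one possible arm for it.

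**Enumeration.** A block has 4! / (2! × 2!) = 6 equally likely orders.

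| Order | Predictable, formed singly | Predictable, formed in pairs | Predictable, all four together |
|---|---|---|---|
| NNCC | 2 (third, fourth) | 2 | 0 |
| NCNC | 1 (fourth) | 0 | 0 |
| NCCN | 1 (fourth) | 0 | 0 |
| CNNC | 1 (fourth) | 0 | 0 |
| CNCN | 1 (fourth) | 0 | 0 |
| CCNN | 2 (third, fourth) | 2 | 0 |
| Mean per block | 8/6 = 1.33 | 4/6 = 0.67 | 0 |

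**Over two blocks.**
- Formed singly: mean 2 × 8/6 = 2.67, range 2 to 4. P(2) = (4/6)² = 0.44, P(3) = 2 × (4/6) × (2/6) = 0.44, P(4) = (2/6)² = 0.11.
- Formed in pairs: mean 2 × 4/6 = 1.33, range 0 to 4. P(0) = 0.44, P(2) = 0.44, P(4) = 0.11.
- Whole block together: 0.

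**Partial knowledge, formed singly.** The chance that the best guess is right is 1/2 for the first group, 2/3 for the second, 1/3 × 1 + 2/3 × 1/2 = 2/3 for the third and 1 for the fourth. That sums to 2.83 per block, or 5.67 of 8 groups, against 4 by chance.

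**Comparator.** A single 4:4 list of eight, formed singly, still leaves at least 1 predictable group, and 1.6 on average.

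**Which case applies.** There is one recruiting site, women must have enrolled in its programme within 6 months, and recruitment began in January 2019. Forming a whole block at once would need 4 × 9 = 36 to 4 × 12 = 48 such women together. That makes sequential formation plausible but does not establish it. Control sessions share days and times with NEAT sessions (Active control intervention), so concurrent groups remain possible.

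**Consequence for the effect estimate.** If selection shifted the mean change in one group by s SD, its arm mean, and hence the arm difference, would move by s/4. The article gives no basis for s. For assumed values of 0.2, 0.4 and 0.8 SD, the shift is 0.05, 0.1 and 0.2 SD, against the stated margin of error of 0.43 to 0.70 SD.

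**The case against.** The strongest reply is that nothing in the article says groups are formed one at a time. A reader might infer that the arms of at least two groups are known while unblinded investigators are taking consent. The text does not support that. The guaranteed minimum is 0 if groups form in pairs or a block at a time. Consent may be taken by the research coordinator, whose knowledge of earlier arms is not described, and no passage says that the person taking consent also delivers sessions. This stands, so the point is conditional.

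A reader might also take the list made before enrolment as a leak. It is not one. A statistician outside enrolment and delivery generates it and it is held securely, which is sound practice. The route described here is deduction from earlier groups.

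The harm is also undocumented. No procedure for deferring women is described, and the single site, the 6-month window and the need to fill groups all limit discretion. The outcome is change from baseline, so selection would have to predict change and not only baseline level. This too stands: the bias cannot be sized, and a reader should not take 0.1 SD, or any other figure, as an estimate of it.

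Finally, roster procedures are often left to a full protocol, and their absence is no fault in itself. But the article makes a blinding statement covering all research staff, and the fixed block it describes can make that statement untrue. That goes beyond missing detail.

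**Conclusion.** The concern holds conditionally. If groups are formed one after another and each arm is revealed before the next group is recruited, two to four of the eight arms (mean 2.67) can be deduced before consent. The blinding statement then cannot be relied on for those groups. With concurrent pairs the count is 0 to 4 (mean 1.33), with a probability of 1 − 0.44 = 0.56 that at least two are predictable. With whole blocks formed together there is no problem.

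The count assumes that someone involved in recruitment knows the block size and the earlier arms. The article makes that possible, since a principal investigator may take consent and the investigators who deliver the intervention are unblinded. It does not state that it happens. Whether any selection occurred, and how large its effect would be, cannot be told from the document. The sample size figures are unaffected.

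**What to change.** **Groups not yet allocated.** Fill each group strictly in order of consent date. Close a dated roster, with consent, eligibility and baseline complete for every member, before that group's allocation is opened. Filling in consent order removes most of the discretion over who joins, even where the arm could be guessed. Where existing staffing allows, have consent taken by a team member who does not deliver the intervention and is unaware of earlier allocations; the article does not show that the coordinator meets this description.

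**Groups already allocated.** Report the order in which groups were formed and the date each roster closed relative to the opening of its allocation. Qualify the blinding statement so that it does not claim more than the block design allows.

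**Block size.** Changing it is optional. It trades off against calendar balance, and forced 1:1 balance over eight groups still leaves some predictability (mean 1.6 with a single list of eight, against 2.67).

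**Cost.** A few sentences of procedure and a dated roster, with no extra staff. The small downside is less flexibility in scheduling women into groups.
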